**Methods/design:**

The design is a cluster-randomized controlled pilot and feasibility trial. Chiropractors in private practice in Canada will be approached to participate in the study. Thirty consenting chiropractors will be randomized to receive either a theory-based educational intervention in the experimental group or simply a printed copy of the guideline in the control group. Each chiropractor will recruit five neck pain patients (a total of 150 patients) into the study. Development of the multifaceted intervention was informed by the results of a related qualitative study based on the Theoretical Domains Framework and consists of a series of three webinars, two online case scenarios, a self-management video on Brief Action Planning, and a printed copy of the practice guideline. *Primary feasibility outcomes* for both chiropractors and patients include rates of (1) recruitment, (2) retention, and (3) adherence to the intervention. A checklist of proxy measures embedded within patient encounter forms will be used to assess chiropractors’ compliance with guideline recommendations (e.g. exercise and self-care prescriptions) at study onset and at 3 months. Secondary outcomes include scores of behavioural constructs (level of knowledge and self-efficacy) for recommended multimodal care. *Clinical outcomes* include pain intensity and neck pain-specific disability. Analyses from this study will focus on generating point estimates and corresponding 95 % confidence intervals for parameters of a priori interest (recruitment, retention, adherence, pain intensity, Neck Disability Index).

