### Specific objectives

The specific objectives target two groups of participants: chiropractors and patients. For each group, both feasibility and efficacy potential will be estimated.For chiropractors, the feasibility objectives are to estimate the proportion who Are eligible to participate and are willing to be randomized; Comply to all study procedures, including completing the KT intervention component and implementing the CPG recommendations; and Complete the 3-month follow-up evaluation.
For patients, the feasibility objectives are to estimate the proportion who Are eligible to participate and are willing to be randomized; Adhere to all study procedures; and Complete the 3-month follow-up visit and all questionnaires.
For chiropractors, the efficacy potential objectives are to estimate The extent to which knowledge and self-efficacy changes after engaging in the KT intervention and CPG and The extent to which knowledge and self-efficacy changes after engaging in CPG.
For patients, the efficacy potential objective is To estimate the effect of their chiropractor’s KT intervention and CPG implementation changes in pain, disability, and satisfaction with care at the initial phase, as well as after 3 months of follow-up.
Other secondary objectives are to identify and provide solutions to Chiropractors’ concerns about the quality of the webinars; Potential impediments to successful initiation of the main study protocol after randomization; and Challenges that participating clinicians have with managing the study (e.g. with implementing the multimodal care and/or completing initial and follow-up questionnaires).

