### Statistical analysis

The main analysis will focus on descriptive statistics relating to feasibility to estimate likely recruitment and retention rates, adherence to the intervention, and provide key parameters, e.g. effect size needed to decide on a primary outcome and to estimate the sample size for a full-scale study. Also, we will estimate the potential efficacy of the intervention on adherence to the recommended multimodal approach for NSNP and on patient outcomes of pain and disability. Instead of calculating an average response on each measure for each group and comparing means between groups, this study will identify the proportion of people in each group making a treatment response, which will then be compared between groups. Each person will be classified as having made a response, a deterioration, or no change on each measure based on a change equal to or greater than the MCID published or recommended for that measure. Table 4 provides the summary of this analysis.

**Table 4 Tab4:** Statistical analysis

Construct	Measure	Measurement scale
Feasibility of recruitment, retention, and data completion (both chiropractors and patients)	Recruitment and retention rates, missing data	Descriptive statistics: mean and SD for continuous variables and proportions for categorical variables
Chiropractor process outcomes		
Adherence rate	Single indicators	Continuous data (number of DCs adhering to the intervention per number of eligible participants)
	Composite	Count of indicators reaching “success” threshold
Behavioural	Level of knowledge and self-efficacy	5-point Likert scale (from 1 = strongly agree to 5 = strongly disagree), ordinal
Patient health outcomes		
Pain	Visual analogue scale	Self-rated level of pain on 11 points, continuous
Disability	Neck Disability Index	Scale range and subscales: 10 items in total; each item is scored from 0 to 5 (“0” = no disability and “5” = full disability) for a total of 50
Satisfaction with care	Questionnaire	Self-rated satisfaction with care measured on the short-form questionnaire rated on a 5-point Likert scale from “very satisfied” to very “dissatisfied”
Potential efficacy	Post-intervention between groups	Normal approximation to the binomial

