For the efficacy potential analysis, we will estimate the proportion of chiropractors who endorsed a higher knowledge level post-intervention in the control group and use this as the basis for calculating the probability of achieving a response more extreme than this in the intervention group using the normal approximation to the binomial distribution (stattrek.com). For example, if 2 of 15 participants in the control group endorse a higher knowledge level, this yields an expected “success” proportion of 0.13. Based on this expected proportion or probability, if 5 or more of the 16 chiropractors in the intervention group endorsed a higher knowledge response, the probability of this occurring by chance would be 0.047. This approach will be used for each of the single indicator variables under study here (i.e. knowledge and self-efficacy).

We will use generalized estimating equations (GEEs) to adjust for anticipated correlation in measurements of observations within practices (clusters). For pain and disability, GEE will be used separately for each of these outcomes and to examine for any effect of our complex intervention over time (the follow-up period). This method extends the standard regression analysis to account for any covariance between repeated measurements of pain and disability (as separate outcomes) over time, in addition to accounting for anticipated correlation of observations within practices.

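### Chiropractor knowledge and self-efficacy are 5-point ordinal items, but the stated comparison counts only those endorsing a higher level, so it cannot give the extent of change that the objectives ask for

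*Protocol article*

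**What the plan says.** All references are to the protocol article.

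- **Objective.** For chiropractors in the intervention arm, Specific objectives asks for "The extent to which knowledge and self-efficacy changes after engaging in the KT intervention and CPG". A parallel objective covers those who receive the guideline only.
- **Outcome.** The abstract states: "Secondary outcomes include scores of behavioural constructs (level of knowledge and self-efficacy" (the parenthesis closes after these words). Table 4 gives the scale as "5-point Likert scale (from 1 = strongly agree to 5 = strongly disagree), ordinal".
- **Timing.** Table 2 lists these questionnaires at baseline and 3 months. The text under Measures places the chiropractor questionnaire at study end.
- **General rule.** Statistical analysis sets group averages aside: "Instead of calculating an average response on each measure for each group and comparing means between groups". It uses responder proportions in their place, and adds: "Each person will be classified as having made a response, a deterioration, or no change on each measure".
- **Chiropractor comparison.** The efficacy potential analysis states that "we will estimate the proportion of chiropractors who endorsed a higher knowledge level post-intervention in the control group", and takes this proportion as the basis for a tail probability in the intervention arm. Its example begins "if 2 of 15 participants in the control group endorse a higher knowledge level". It extends the method to both constructs: "This approach will be used for each of the single indicator variables under study here (i.e. knowledge and self-efficacy".
- **Other analyses.** The generalized estimating equations are described for pain and disability. The abstract's list of parameters to be estimated with 95% confidence intervals does not include knowledge or self-efficacy.

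**The concern.** The objective is about amount and the stated analysis is about count. The proportion endorsing a higher level says how many chiropractors moved, and nothing about how far. The same section says that the pilot should supply an effect size for choosing a primary outcome and sizing the main trial. For these two outcomes the stated output is a proportion and a tail probability, from which neither a mean difference, nor a standard deviation, nor an odds ratio over the five categories can be recovered.

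This is a stated choice and not a detail left to a fuller document: averages are expressly replaced by responder proportions, and the chiropractor comparison is then fixed in that form. It affects secondary outcomes measured on the unit that is randomized, where the numbers are small and each 5-point response carries information that the cut discards.

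**Working it through.** **1. The plan's own figure.** Inputs from Statistical analysis: control 2/15 = 0.13; intervention 5 or more of 16; stated probability 0.047. The exact binomial tail P(X ≥ 5 | n = 16, p = 0.13) is 0.0471, so the figure reproduces. It is not the normal approximation that the text names, which gives 0.0150 without and 0.0360 with continuity correction.

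**2. What the count cannot distinguish.** Three hypothetical intervention arms of 16:

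| Pattern | Endorsed higher | Tail probability | Mean gain in steps |
|---|---|---|---|
| 5 up one step, 11 unchanged | 5/16 | 0.047 | 5/16 = 0.31 |
| 5 up three steps, 11 unchanged | 5/16 | 0.047 | 15/16 = 0.94 |
| 5 up one step, 5 down one step, 6 unchanged | 5/16 | 0.047 | (5 − 5)/16 = 0 |

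The comparison returns the same answer for all three. The three-way classification would separate the third from the first, but the comparison does not use it. Nothing in the stated analysis separates the first from the second.

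**3. Ceiling, under one reading.** If higher means higher than the chiropractor's own baseline, anyone already in the most favourable category cannot be a success. With a share c there, the largest attainable proportion is 1 − c: 93% for an assumed c of 7%, and 72% for an assumed 28%. The article gives no baseline distribution. If the endpoint is simply the post-intervention level, this limit does not arise.

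**4. Numbers available.** The target is 30 chiropractors, about 15 per arm. Trial status reports 45 randomized, so 22 to 23 per arm, and 45 × 0.80 / 2 = 18 per arm at the expected retention.

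**5. Precision, illustrative only.** Assumed model: a standard normal latent score cut at −1.5, −0.5, 0.5 and 1.5 into five categories, a given correlation between baseline and 3 months, and a latent shift in the intervention arm. Tests are two-sided at 5%. The gain is adjusted score minus two-proportion z, in percentage points.

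| Per arm | Correlation | Shift (SD) | z on improved | Wilcoxon on change | Baseline-adjusted score | Gain |
|---|---|---|---|---|---|---|
| 15 v 15 | 0.5 | 0.5 | 16.6% | 19.8% | 27.9% | 11.3 |
| 15 v 15 | 0.5 | 0.8 | 34.0% | 43.9% | 58.6% | 24.6 |
| 15 v 15 | 0.5 | 1.0 | 49.6% | 62.5% | 78.6% | 29.0 |
| 15 v 15 | 0.7 | 0.8 | 49.6% | 61.3% | 72.1% | 22.5 |
| 15 v 16 | 0.9 | 0.8 | 87.8% | 90.8% | 94.2% | 6.4 |
| 18 v 18 | 0.5 | 0.8 | 46.3% | 52.8% | 69.5% | 23.2 |
| 18 v 18 | 0.7 | 0.8 | 64.6% | 71.7% | 81.4% | 16.8 |
| 22 v 22 | 0.5 | 0.8 | 49.4% | 63.4% | 77.5% | 28.1 |

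With no shift, the z test, the Wilcoxon test and the adjusted analysis reject in about 4% to 6% of runs. A second model, tuned to the example's 13% and 31% improving (15 v 16), gives z 22.9% and adjusted score 30.3% with a symmetric baseline, a gain of 7.4 points. With 28% at ceiling it gives 23.7% and 34.5%, a gain of 10.8 points.

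**6. The plan's own rule is different.** The stated method treats the control proportion as known and takes one tail. By enumeration at 15 v 16 with a 0.05 cut-off (a zero control count taken as rejecting on any success), it rejects in 49% (exact tail) to 62% (normal approximation) of trials at 13.3% v 31.25%. It also rejects in 15% to 22% when both arms have 13.3%. The z column above therefore does not describe it.

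**The case against.** The responder approach is deliberate and openly stated, a percentage is easy to read, and this is a pilot whose main analysis is descriptive. No significance level or power is stated for this comparison, and in the example-based model the gain over a z test is modest. All of this stands, which is why power is secondary here. It does not answer the mismatch: a deliberate count still does not estimate an extent.

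Three stronger readings are tempting, and the documents do not support them.

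- **A reader might infer that the planned comparison has only about 23% power.** That figure belongs to a two-sided two-proportion test, which the plan does not name. The plan's rule rejects too often, including when there is no difference. That is a separate fault and should be handled as one.
- **A reader might infer that deterioration is lost altogether.** The general rule does classify it. Only the chiropractor comparison leaves it out.
- **A reader might infer that chiropractors at the top category can never succeed.** That holds only if the reference is baseline. Table 4 describes the efficacy comparison as post-intervention between groups, and Measures places the questionnaire at study end, so the reference is not settled.

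The remedy has limits too. A linear model treats an ordinal item as interval, and a proportional-odds model over five categories may meet sparse cells with about 18 per arm.

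**Conclusion.** The concern holds as a mismatch between objective and analysis. Knowledge and self-efficacy are ordinal scores, the objectives ask for the extent of change, and the only between-arm analysis stated for them is a proportion that carries no size of change and no effect size on the score scale. This needs no assumptions beyond the text.

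The precision argument is supporting only. With 15 or 16 per arm, the baseline-adjusted score gains about 6 to 29 percentage points over a valid two-proportion test, and the gain is still there at about 18 per arm. The range rests on an assumed latent-normal model, assumed correlations of 0.5 to 0.9 and assumed shifts of 0.5 to 1.0 SD, none of which the article gives. The ceiling effect depends both on the reading of higher and on an unknown baseline distribution. The outcomes are secondary and the trial is a pilot, so this is an inexpensive improvement and does not threaten the feasibility objectives.

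**What to change.** In the efficacy potential paragraph of Statistical analysis and in Table 4:

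1. Make the between-arm analysis of knowledge and self-efficacy a comparison of the full 1-5 score at 3 months adjusted for the baseline score, by ANCOVA or a proportional-odds model. Report the adjusted mean difference or odds ratio with a 95% confidence interval. State the direction of scoring, since 1 is strongly agree.
2. If no baseline was collected, compare the 3-month scores between arms with a Wilcoxon test.
3. Keep the percentages improved, unchanged and deteriorated by arm as a descriptive supplement.
4. Reconcile Table 2 (baseline and 3 months) with the text under Measures (study end) on when the chiropractor questionnaire is given. This decides whether item 1 or item 2 applies.

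The cost is wording only. No new participants are needed, and no new data beyond what Table 2 already schedules. The downside is that a score difference on a Likert item is less intuitive than a percentage, and ANCOVA treats the item as interval. The retained percentages ease the first, and the proportional-odds option avoids the second.

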#### Missing data

Missing data will be assumed not to be at random, especially if there are differential losses to follow-up between groups. However, no imputation of missing data is planned.

#### Dissemination of results

The results of the study will be published in a peer-reviewed journal and presented at the CCA National Convention. The study will be reported using the Consolidated Standards of Reporting Trials (CONSORT) diagram (Fig. 1). A summary of the study results will also be saved at ClinicalTrials.gov to allow general access to obtain findings.

**Fig. 1 Fig1:**
[figure not shown]
CONSORT participant flow diagram

## Discussion

We propose to determine the feasibility of evaluating a KT intervention in chiropractic clinical practice designed to improve the management of NSNP. The primary purposes of a feasibility study are to ensure that study implementation is practical and to reduce threats to the validity of a larger fully powered study [43]. This study is primarily a feasibility study with feasibility objectives. As a “small-scale” version of a planned main study, this study also constitutes a pilot study aimed at testing whether the components of the main study can all work together.

A full-scale randomized controlled trial in Canada would aim to determine whether the use of multimodal care in patients with NSNP reduces the pain and cost of treatment. A confirmatory trial should provide key insights on the effects and advantages of the use of multimodal care by chiropractors on patient health outcomes (e.g. pain, physical functioning, disability, and satisfaction with care) and inform health service-related research questions and interventions that could be translated into existing health care systems. A better understanding of the effective components of multimodal care, and the effective implementation of CPGs in general, should help future researchers and chiropractors to design and implement complex KT interventions and multimodal care aimed at maximizing the uptake and utilization of evidence in the management of patients with NSNP.

### Study limitations

Given the nature of the study, we will be unable to determine which individual components of the intervention will be effective or ineffective or to quantify the number of modalities administered to individual patients. Recruitment is always a concern in clinical studies, and we anticipate difficulty with participation from busy, community-based private chiropractors. Hence, we are aware that it is important to establish the feasibility of conducting the current study within private chiropractic practices in Canada before progressing to the full-scale study. Meeting this objective is necessary for the purposes of future funding applications for our planned main study.

### Relevance to practice

We are not aware of published studies on the successes and failures of previous attempts to implement a multifaceted KT strategy aimed at improving the management of NSNP by chiropractors. The conduct of this feasibility study is expected to be compatible with existing infrastructure while permitting a certain degree of flexibility and adaptation to the needs and routines of individual community-based clinicians. In the current pilot portion of the study, we will test chiropractors’ adherence to (and therefore tolerance of) a study protocol aiming to both confirm the effectiveness and increase the use of multimodal care (a combination of manual therapy, self-management advice and support to patients, and promotion of physical activity including exercise) for patients with NSNP in a future main study.

Our future main study will also provide insight into the effect of multimodal care on physical functioning, quality of life, and other outcomes important for patient and provider decision-making. It will serve as a template for additional trials of knowledge implementation and complex evidence-based chiropractic intervention studies. While the proximate goal is to improve chiropractors’ receptiveness to and utilization of research evidence in private practice, the ultimate goal is to optimize the outcomes of patients managed by chiropractors, both for NSNP specifically and for other musculoskeletal conditions in general in the community.

### Trial status

At the time of writing, 45 chiropractors have agreed to participate in the study and have been randomized to the intervention and control groups. Participants have started recruiting neck pain patients. Results are expected in May 2016.

## Abbreviations

BAP, Brief Action Planning; CCA, Canadian Chiropractic Association; CPGs, clinical practice guidelines; KT, knowledge translation; NDI, Neck Disability Index; NSNP, non-specific neck pain; PSQ-18, Patient Satisfaction Questionnaire; TDF, Theoretical Domains Framework; VAS, visual analogue scale
